## 3.2 Primary and secondary endpoints (outcomes, outcome measures, Zielgrössen)

Endpoints are understood as significant changes in outcome measures (see 5.2 for Feature Description for further details)

(Ep) Primary endpoint: significant difference between mean MWT- and DS-MWT-latencies.

Additional, secondary, exploratory endpoints are

(Es-1) significant differences in driving parameters

(Es-2) significant differences in ET- and EEG-features

(Es-3) significant differences in @home-PSG-recordings and test sequence

(Es-4) significant correlation to biomarkers for sleepiness in saliva and/or exhaled breath

See 5.1.2 for statistical analysis plan

## 3.3 Study design

This study is a monocentric, controlled, within-subjects, randomized, cross-over clinical trial on a cohort of OSAS patients. Two equivalent arms explore the influence of the test sequence per starting condition. Neither participants nor observers can be fully blinded.

Allocation to the starting condition (W or C) and one of two study arms (DM or MD) determining measurement sequence is required and will be randomized (lottery).

*A priori,* we do not allocate or stratify by study population characteristics, i.e., according to sex, age, medication, dosage, duration of treatment etc. We will, however, evaluate *post hoc*, whether outcomes are influenced by these factors.

## 3.4. Study intervention

Intervention: Withdrawal of CPAP-treatment for ≥ 7d

# Study POPULATION and Study procedures

## 4.1 Inclusion and exclusion criteria, justification of study population

The total sample size is N_total_ = 54, consisting of the intervention group N_I_ = 36 and a healthy comparison group N_H_ = 18.

For the intervention group, we will recruit from a highly adherent pool of patients with OSA treated in the Sleep Disorders Center and Pulmonary Division, University Hospital of Zurich, Zurich, Switzerland. For the comparison group (healthy adults), we will recruit from the public.

The restricted pool for the study population has the advantage that it is highly coherent in treatment and supervision. Members of the pool are already preselected by the referring partner institution (Sleep Disorders Center) for not having a.) substantial comorbidities (such as major affective, somatic or neurological disorders) or cognitive deficits and b.) any additional risks caused by the intervention, i.e. CPAP-withdrawal.

We will not be able to, at this point, ensure gender balance, which is due to the much higher prevalence of OSA in the male population. While there is the chance of having a balanced pool, a retrospective stratification seems out of scope due to the sample size and the between-patient variability of the outcome measures in the intervention group.

Inclusion criteria (OSA patients):

- adult driver
- diagnosed OSA,
- established CPAP-treatment regime, highly adherent and compliant within the last 6 months (>5h, >80% of days),
- at impaired eyesight with more than +/- 5 diopter or astigmatism, contact lenses are required (for eye tracking)

Inclusion criteria (healthy comparison croup):

- adult driver
- no declared psychiatric disorders,
- no declared sleep-related diagnosis,
- at impaired eyesight with more than +/- 5 diopter or astigmatism, contact lenses are required (for eye tracking)

Exclusion criteria (for both groups):

- sensibility to motion sickness (kinetosis, dizziness, etc. in 5 min screening drive),
- professional drivers (if working during the study period),
- inability to understand the study procedure for linguistic or cognitive reasons.

Based on the inclusion criteria and the preselected pool for recruitment, we will not include any vulnerable participants as defined to the Swiss HRA (chapter 3, i.e. children, adolescents, adults lacking capacity, or prisoners). However, participation in the experimental procedure does not pose any additional risks for pregnant women, neither for patients, healthy adults or the unborn child. Therefore, the participation of pregnant individuals is possible and a pregnancy test is not required.

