| **Inclusion- / Exclusion Criteria** | Inclusion criteria (OSA patients):   - adult driver - diagnosed OSA, - established CPAP-treatment regime, highly adherent and compliant within the last 6 months (>5h, >80% of days), - at impaired eyesight with more than +/- 5 diopter or astigmatism, contact lenses are required (for eye tracking)   Inclusion criteria (healthy comparison croup):   - adult driver - no declared psychiatric disorders, - no declared sleep-related diagnosis, - at impaired eyesight with more than +/- 5 diopter or astigmatism, contact lenses are required (for eye tracking)   Exclusion criteria (for both groups):   - sensibility to motion sickness (kinetosis, dizziness, etc. in 5 min screening drive), - professional drivers (if working during the study period), - inability to understand the study procedure for linguistic or cognitive reasons.   Based on the inclusion criteria and the preselected pool for recruitment, we will not include any vulnerable participants as defined to the Swiss HRA (chapter 3, i.e. children, adolescents, adults lacking capacity, or prisoners). However, participation in the experimental procedure does not pose any additional risks for pregnant women, neither for patients, healthy adults or the unborn child. Therefore, the participation of pregnant individuals is possible and a pregnancy test is not required. |
| **Number of Participants with Rationale** | The total sample size is N_total_ = 54, consisting of the intervention group N_I_ = 36 and a healthy comparison group N_H_ = 18.  For sample size calculation (see chapter 5.1.1)  For the intervention group, we will recruit from a highly adherent pool of patients with OSA treated in the Sleep Disorders Center and Pulmonary Division, University Hospital of Zurich, Zurich, Switzerland. For the comparison group (healthy adults), we will recruit from the public.  The restricted pool for the study population has the advantage that it is highly coherent in treatment and supervision. Members of the pool are already preselected by the referring partner institution (Sleep Disorders Center) for not having a.) substantial comorbidities (such as major affective, somatic or neurological disorders) or cognitive deficits and b.) any additional risks caused by the intervention, i.e. CPAP-withdrawal. |
| **Study Intervention** | Withdrawal of CPAP-treatment for ≥ 7d |
| **Control Intervention** | n.a. |

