## 6.5 Pregnancy (if applicable)

n.a. since there is no known risk arising from the intervention or study procedure with respect to pregnancy, pregnancy is not an exclusion criterion and will not be handled differently in the analysis.

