## 7.2 Risk-benefit assessment

The participation in this study involves only minimal risks (category A). The study procedures at each one of 7 visits consist of standardized and mostly non-invasive tests. Participants are under constant supervision.

In rare cases, the use of the driving simulator can lead to dizziness and discomfort (simulator sickness), but these quickly subside when leaving the simulator or completing the test.

EEG-mounting and blood sampling by means of peripheral venous donor catheter will be conducted by trained personnel. Hematoma from blood sampling and/or skin irritations from EEG electrodes may occur rarely, but these usually disappear without further complications. The collected full blood volume of 9ml ml is generally considered harmless to health. There are no health risks in the sampling of urine, saliva, dried blood spots, and exhaled breath.

For the intervention “CPAP-withdrawal” (W), participants omit their overnight use of CPAP-treatment at home for a ≥7-day-period (typically holidays) and thus will have a reactivation of OSA. This intervention has been validated as a safe, effective and well-controlled model to study the pathophysiological consequences of OSA (3, 4). All patients will be primarily assessed by physicians from the Sleep Disorders Center on whether a CPAP-withdrawal can cause them health risks. Only preselected patients with no risks to their health will be included in the study. At the end of the study, patients will resume their established long-term CPAP therapy. Professional drivers will be excluded from the study, if working during the study period.

Otherwise, participation in the study is not associated with any known specific risks.

There is no direct health benefit for the study participants.

Overall social and scientific benefits are described in section 7.1.

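### The protocol declares no pregnancy risk from participation, CPAP withdrawal included, while the physician withdrawal-risk assessment is worded for the patient's own health only

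*Protocol*

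**What the plan says.** Section 4.1 of the protocol gives the eligibility position: "participation in the experimental procedure does not pose any additional risks for pregnant women, neither for patients, healthy adults or the unborn child". The synopsis row on inclusion and exclusion criteria carries the same sentence, and both draw the consequence: "Therefore, the participation of pregnant individuals is possible and a pregnancy test is not required". Neither place cites a source.

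Section 6.5 returns to the subject: "n.a. since there is no known risk arising from the intervention or study procedure with respect to pregnancy, pregnancy is not an exclusion criterion". It also cites nothing.

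Section 3.4 defines the intervention: "Withdrawal of CPAP-treatment for ≥ 7d". Section 7.2 and the synopsis row on risk and benefit say that patients in this condition "thus will have a reactivation of OSA". Both describe withdrawal as a validated, safe model and cite references 3 and 4 for it.

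Two safeguards address withdrawal risk. Section 4.1 says the patient pool has already been preselected by the referring centre for not having "any additional risks caused by the intervention, i.e. CPAP-withdrawal". Section 7.2, with its synopsis copy, adds: "All patients will be primarily assessed by physicians from the Sleep Disorders Center on whether a CPAP-withdrawal can cause them health risks". It then restricts inclusion to patients for whom no risk to their own health was found.

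**The concern.** The admission of pregnant OSA patients is a positive eligibility decision with a stated reason, so this is not a detail left to another document. The reason is a flat statement of no added risk, to the mother or the unborn child. The protocol nevertheless says that its intervention brings a treated disease back, and it considers individual medical clearance necessary before withdrawal. The clearance concerns the patient. Risk to an unborn child is therefore assumed absent in one place and not assessed in the other.

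At stake is the safety footing of a decision to let a pregnant patient stop an established therapy for a week or more. Section 7.2 concedes: "There is no direct health benefit for the study participants". The claim of no risk therefore has to stand on its own, with no benefit to the participant to set against it.

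**Working it through.** There is no figure of the plan's to reproduce. The check sets the statements side by side.

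1. **Does the no-risk statement cover the intervention?** Section 4.1 speaks of the experimental procedure, which could mean only the tests and sampling. Section 6.5 settles the question by naming the intervention alongside the study procedure. Section 6.5 is also weaker: it says that no risk is known, whereas section 4.1 says that none is posed.

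2. **What is the intervention?** Section 3.4: CPAP withdrawal for at least 7 days. Section 7.2 and the synopsis: OSA is reactivated. The statement in section 6.5 therefore covers a period of reactivated disease.

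3. **Is a source given?** None is given in section 4.1, its synopsis copy or section 6.5. References 3 and 4 are cited in section 7.2 and the synopsis for withdrawal as a model in OSA generally. The protocol does not tie them to pregnancy, and whether they cover it cannot be checked from the documents.

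4. **Do the safeguards reach the unborn child?** The preselection in section 4.1 is worded openly, for any added risk from withdrawal, and names neither pregnancy nor the unborn child. The physician assessment in section 7.2 is also open as to which conditions count, but it is worded for health risks to the patients themselves, and so is the inclusion rule that follows it.

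5. **Does the timing fit?** Preselection is described as already done. By section 4.3, patients who start with withdrawal stop CPAP between visits 1 and 2. Those who start with continuation stop between visits 4 and 5. Each interval is at least 7 days and may be longer. A clearance given earlier need not reflect a pregnancy present when withdrawal begins.

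6. **Who could be affected?** Total 54, healthy comparison group 18, so 54 − 18 = 36 OSA patients undergo withdrawal. This is only a ceiling. Section 4.1 notes the much higher prevalence of OSA in men, and section 7.1 expects a gender imbalance for that reason. The documents give no count of women or of pregnancies, so the affected subset cannot be estimated.

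**The case against.** The strongest reply is that nothing here is shown to be false. Section 6.5 says only that no risk is known, and no statement in the protocol contradicts that. Section 4.1 introduces its pregnancy text by reference to the preselected pool, so the no-risk claim can be read as applying to patients already cleared for withdrawal. Every patient must pass a medical assessment. That assessment names no specific condition, so the absence of pregnancy from it is not peculiar. A medical-history questionnaire is taken at visit 1; its items are not shown and may include pregnancy. Section 6.2 counts a congenital anomaly or birth defect as a serious adverse event, so a bad fetal outcome would be reported.

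Much of this stands. Three stronger readings are tempting, and the documents do not support them:

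- **That withdrawal endangers a pregnancy.** A reader might infer this from the reactivation of OSA. The protocol contains no evidence on the point and describes withdrawal in general as safe.
- **That a pregnant OSA patient would go into withdrawal unchecked.** She must still pass the physician assessment, which may well detect a risk to her.
- **That two thirds of the sample is exposed.** The ratio 36/54 is the share of OSA patients and says nothing about pregnancies.

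What the reply does not remove is narrower. The gate is worded for the patient's health, and the only mention of the unborn child is the unsourced statement that there is no risk. Classing a birth defect as a serious adverse event provides for reporting after the event; it does not assess risk before withdrawal.

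**Conclusion.** The point holds in a limited form. The protocol justifies admitting pregnant OSA patients with an unsourced no-risk statement that section 6.5, in weaker words, extends to CPAP withdrawal, while the physician assessment of withdrawal risk is worded for the patient's own health only. Following the text as written leaves risk to the unborn child assumed absent.

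The size is small: an uncountable subset of 36 patients, expected to be mostly men. The primary comparison, sample size and power do not change. The conclusion rests on reading the assessment in section 7.2 as worded, and on taking intervention in section 6.5 to mean what section 3.4 defines. It does not depend on withdrawal being harmful in pregnancy, which the documents leave open, and it gives no ground for a pregnancy test or a general exclusion.

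**What to change.** - In section 4.1, its synopsis copy and section 6.5, limit the no-risk statement to the test and sampling procedures, so that it no longer covers CPAP withdrawal.
- In section 7.2 and the synopsis row on risk and benefit, state that the existing physician assessment considers known or self-reported pregnancy, including risk to the unborn child, before the withdrawal period starts, whether that is the first or the second phase.

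The cost is wording in five places. No new visit or test is needed, and no analysis changes. The only downside is that possibly a very few patients would not be enrolled.

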## 4.2 Recruitment, screening and informed consent procedure

For the intervention group, we will recruit patients with OSA from a highly adherent preselected pool treated in the Sleep Disorders Center and Pulmonary Division, University Hospital of Zurich, Zurich, Switzerland. For the comparison group, we will recruit from the public.

Recruitment towards and up until inclusion will be accomplished by personal communication by phone, email, in a video call (optional) or in person at the study site.

First contact will be offered by a flyer containing contact information to the investigators.

Investigators will offer to explain details of the study either by phone, email, or a video call (optional) to the participants (either individually or in groups). If participants are interested, a first on-site visit is scheduled.

Investigators will explain to each participant the nature of the study, its purpose, the procedures involved, the expected duration, the potential risks and benefits and any discomfort it may entail.

Each participant will be informed that participation in the study is voluntary and that he or she may withdraw from the study at any time and that withdrawal of consent will not affect his or her subsequent medical assistance and treatment.

All participants for the study will be provided with a participant information sheet and a consent form describing the study and providing sufficient information for participants to make an informed decision about their participation in the study. Enough time as much as the participant desires will be given to decide whether to participate or not.

The formal consent of a participant, using the approved consent form, will be obtained before the participant is submitted to any study procedure.

The consent form will be signed and dated by the sponsor-investigator or his designee at the same time as the participant signs. A copy of the signed informed consent will be given to the study participant. The consent form will be retained as part of the study records.

The informed consent process will be documented in the patient file and any discrepancy to the process described in the protocol will be explained. The informed consent will be obtained from the participant at the first study visit before biological samples of blood and urine are collected and which obtained data will be used for further studies.

A 5-min-long screening drive will evaluate the only exclusion criterion (kinetosis, dizziness) and ensure a full understanding of the following task.

Participants will have no direct benefit from the study. As participation in a research project with no expected direct benefit may be appropriately remunerated, there will be a financial compensation. However, participants indirectly benefit form repeated measures of their sleep quality (PSG) that could otherwise not be performed in standard care situations. In addition, OSA patients indirectly benefit from getting to know their individual effects upon CPAP-withdrawal. Upon request, the collected information will be available for their further personal use for all participants.

According to the [Leitfaden Finanzielle Zuwendungen](https://swissethics.ch/assets/pos_papiere_leitfaden/entschaedigungen_pkl_d.pdf), Abschnitt 2 Modell b, we aim to compensate participation with **CHF 500 for the completed study**. An ethical guideline concerning the remuneration of participants is also available on [www.swissethics.ch](http://www.swissethics.ch).

Here we discussed two models for compensation:

Model A: strictly time-proportional, participants receive ca 12.00 CHF/hour spent at the study site.

Model B: content-proportional, participants receive 80 CHF if only visits 2 and 3 are completed, 180 CHF if visits including 4 are completed, 230 CHF if visit 5 including overnight PSG is completed, 350 CHF if visits including visit 6 are completed and the full 500 CHF if all study visits are included. This reflects an hourly compensation increasing from 12 CHF to 35.71 CHF if averaged cumulated over time on task on measurements or from 12 CHF to 20 CHF if calculated individually by time on task per visit.

Model B reflects the potential of increased information gained per completed visit. In addition, calculated increasing hourly rates per individual time on task reflect typical compensations without forcing undesired motivational aspects within the cohort (participation by financial benefit only). The compensation scheme reflects, that there is neither third-party financial benefit nor substantial risks to a participant’s health involved. It might be noted, that studies with similar intervention (3, 4) or higher compromise for the participants (12) did get no or lower compensation, respectively.

Weighing in attrition and stopping (partial reference) biases, we decided to compensate according to **model B**. A remaining risk of incomplete recruitment or increase drop-out within the allocated study period and, thus, potential effects on the power of the study, is acknowledged.

In any case, also the termination during or in between the study visits, participants will have to sign a receipt for the compensation.

## 4.3 Study procedures

The planned overall duration of the study is 24 months, with 01/05/2025 being First-Participant-in (FPFV, anticipated date of the screening/enrolment of the first patient) and 30/04/2027 being Last-Participant-Out (LPLV, anticipated date of the last participant’s final visit. A published manuscript or submission of the final report will be handed in by 30/04/2028.

Figures 1 and 2 as well as Tables 1 and 2 summarize all relevant procedures and study visits.

[figure not shown]

**Figure 1.** Overall course of the study. V = visit, PSG = @home-polysomnography, D = driving simulation-based maintenance of wakefulness test, M = maintenance of wakefulness test. Visit 1 comprises inclusion and a brief screening. Visit 2 and Visit 5 serve merely to mount PSGs.

Visit 1 comprises discussion and signing of the informed consent, inclusion, a brief screening drive to control for screening-based exclusion and the randomization lottery. In visit 2 and visit 5 the EEG-electrodes for @home-PSGs are mounted. PSGs are recorded overnight between visits 2-3, 3-4 and 5-6, 6-7 each. During visit 3, 4, 6 and 7 driving simulation-based maintenance of wakefulness tests (D) or maintenance of wakefulness tests (M) will be performed according to the respective study group, i.e. the randomized allocation of starting condition or sequence, respectively (see Figure 2). Randomization will be achieved by lottery during visit 1. Participants are invited to give feedback after the study (optionally personal or online).

Each driving simulation-based maintenance of wakefulness test (D) or maintenance of wakefulness test (M) in visits 3,4,6, and 7 comprises four 40-min-long sessions (also termed “runs”) with EEG-measurements including video, starting at 9 a.m. 11 a.m. 1 p.m. and 3 p.m.. Prior to each session, participants are asked to indicate their subjective level of sleepiness using the Karolinska Sleepiness Scale 8KSS). In each session, participants are asked to stay awake in a dark environment, either sitting still with open eyes without activation (M) or sitting still in a monotonous night-time car-following task in a driving simulator (D). Each driving simulation-based maintenance of wakefulness tests (D) includes eye tracking. Eye tracking will be included in maintenance of wakefulness tests (M), depending on availability of the instrument. Each session is followed by sample taking (blood, saliva, exhaled breath, dried blood spot). EEG-Electrodes are removed after visits 4 and 7, but checked throughout visits 3, 4, 6 and 7. An optional interview after the study phase is possible, if the patients wish to elaborate on the feedback, late effects, lessons learned, or the daily life effects they encountered after completion of all 7 study visits. Visit 1 requires an estimated presence of 1 hour. Visit 2 and 4 require an estimated presence of 1 hour. Visit 3, 4, 6, and 7 each require an estimated presence of 8 hours, with actual test durations of approximately 4 hours, i.e. four times 40-min log runs and 15 min-long sample taking.

[figure not shown]

**Figure 2.** Overall randomization scheme for the intervention group and the comparison group. W_first_ = Group starting with the sequence in the condition “withdrawal”, i.e. the intervention. C_first_ = Group starting with the sequence in the condition “continuation”. D = driving simulation-based maintenance of wakefulness test, M = maintenance of wakefulness test.

**Table 1.** Overall overview of the visits. Timing between visits 1 and 2 as well as 4 and 5 will have to be ≥ 7 days but can vary, visits 2-4 and 5-7 will have to take place on subsequent days (see also Figure 1).

| **Visit** | **0** | **1** | **2** | **3** | **4** | **5** | **6** | **7** |
| --- | --- | --- | --- | --- | --- | --- | --- | --- |
|  | **pre-study phase** | | **phase I** | | | **phase II** | | |
| **Title** | Recruitment  first and second contact  information  scheduling visit 1 | Written consent  screening  eligibility criteria  randomizing (lottery) | PSG mounting | Test visit | Test  scheduling visit 5 | PSG mounting | Test visit | Test visit, feedback |
| **Time [days]** | <-1 | 0 | ≥ 7 | +1 | +2 | + ≥ 7 | +1 | + 2 |
| **Duration [h]** | 0.5 | ~1 | 1 | 8 | 8 | 1 | 8 | ~8.5 |

**Table 2.** Schedule and summary of each study visit including all planned interventions, tests, questionnaires, and biological sampling. ***** = only after written consent.

| **Interventions and tasks** | **Duration [min]** | **0 (R)** | **1** | **2,5** | **1,4** | **3,4,**  **6,7** | **7** |
| --- | --- | --- | --- | --- | --- | --- | --- |
| First contact (personal communication) by physician investigators | 10 | + |  |  |  |  |  |
| Second contact (offering information in two individual mails and one group mail with invitation to a video call) by study site investigators | 10 | + |  |  |  |  |  |
| Oral and written patient information | 25 |  | + |  |  |  |  |
| Written consent | 5 |  | + |  |  |  |  |
| Inclusion criteria | 5 |  | +**^*^** |  |  |  |  |
| Screening drive | 15 |  | +**^*^** |  |  |  |  |
| Exclusion criteria by screening drive | 5 |  | +**^*^** |  |  |  |  |
| Questionnaire: general demographic data | 5 |  | +**^*^** |  |  |  |  |
| Questionnaire: driving behavior | 5 |  | +**^*^** |  |  |  |  |
| Questionnaire: medical history | 5 |  | +**^*^** |  |  |  |  |
| Randomization (lottery) | 5 |  | +**^*^** |  |  |  |  |
| Scheduling next visit | 5 | + | +**^*^** |  | +**^*^** |  |  |
| Mounting and explanation of PSG | 60 |  |  | +**^*^** |  | +**^*^** |  |
| Session 1/4 (KSS, DS-MWT or MWT, incl EEG and ET) | 45 |  |  |  |  | +**^*^** |  |
| Sampling 1/4 (blood, saliva, exhaled breath, dried blood spots) | 15 |  |  |  |  | +**^*^** |  |
| Break 1 | 60 |  |  |  |  |  |  |
| Session 2/4 (KSS, DS-MWT or MWT, incl EEG and ET) | 45 |  |  |  |  | +**^*^** |  |
| Sampling 2/4 (blood, saliva, exhaled breath, dried blood spots) | 15 |  |  |  |  | +**^*^** |  |
| Break 2 (lunch) | 60 |  |  |  |  |  |  |
| Session 3/4 (KSS, DS-MWT or MWT, incl EEG and ET) | 15 |  |  |  |  | +**^*^** |  |
| Sampling 3/4 (blood, saliva, exhaled breath, dried blood spots) | 75 |  |  |  |  | +**^*^** |  |
| Break 3 | 60 |  |  |  |  |  |  |
| Session 4/4 (KSS, DS-MWT or MWT, incl EEG and ET) | 45 |  |  |  |  | +**^*^** |  |
| Sampling 4/4 (blood, saliva, exhaled breath, dried blood spots) | 15 |  |  |  |  | +**^*^** |  |
| Checking PSG | 15 |  |  |  | +**^*^** | +**^*^** |  |
| Discussion, Outlook and Feedback (opt.) | 30 |  |  |  |  |  | +**^*^** |

As all data are recorded automatically (Silab, SAFE, EEG, ET) and/or without interference from the investigator (questionnaires), we do not expect observer or sequence biases here. Any adherence/reporting bias (e.g. participants incorrectly report their medication status or by-consumption) is controlled for by blood sampling. Attrition and stopping (partial reference) biases are minimized by the compensation scheme.

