- (O_s-5_) We will explore, whether or not – and if yes, which and to which extent – **repeated @home-PSG-measurements** reveal night-to-night variability of OSA-parameters (8) such as, for example, AHI, ODI, ¢SpO2, t<90, and how they correlate to other outcome parameters. CPAP data will be used to control for the adherence to the instructions and for OSA--activation control.
- (O_s-6_) We will explore, whether or not – and if yes, which and to which extent – previously identified potential (proteomic) **biomarkers for sleepiness (9-11) in non-invasive samples** such as saliva, exhaled breath, dried bloodspots (12), correlate to the prior treatment or withdrawal of CPAP and the outcomes of the ESS and KSS.

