## 5.2 Feature description

*Test-Latency:*

Mean MWT- or DS-MWT-latencies are determined by averaging latencies from four max. 40 min test- sessions determined by AASM-criteria (REF,) and previously reported additional/complementary parameters (e.g., sleep accidents with closed eyes, (1)) for the two tests, respectively.

*Driving Parameters*

We will collect multiple driving parameters, such as the standard deviation of lane position, SDLP, the standard deviation of velocity, SDS, number of lane departures, and LD. Collected parameters will also be used as one criterion to determine the sleep-accident-derived latency for the DS-MWT. IDS

*ET Features*

A recent review showed that eye movement features and the sleep-wake predictor model could be used to predict sleepiness (6). For example, the blink rate increases with increased sleep pressure and can be used to assess drowsiness or sleepiness. Other valuable ET metrics (5) for our setting are the saccade latency, saccade peak velocity and smooth pursuit velocity gain, which could also reflect levels of sleep deprivation and extreme sleepiness.

*EEG Features*

EEG recordings are required to determine MWT-latencies, based on precise identification of sleep onset (SO). According to AASM classification, sleep onset is defined as the start of the first epoch scored as any stage other than stage W. In most individuals this will usually be the first epoch of stage N1, characterized by SEM (slow eye movements) and LAMF (low-amplitude, mixed-frequency) in EEG activity. Electrophysiological data collected during both classical MWT and DS-MWT will provide useful additional insights into the sleep-wake transition. For example, microsleep episodes (MSEs), i.e., brief periods of sleep intrusion during wakefulness, may occur even before sleep onset. We will analyze manually- and automatically-detected MSEs (17).

*PSG Features*

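### The Karolinska rating is taken only before each run and the biomarkers only after it, so no rating coincides with a sample for the KSS part of objective O_s-6 (minor)

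*Protocol*

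**What the plan says.** Protocol section 4.3 describes four sessions on each test day, starting at 9 a.m., 11 a.m., 1 p.m. and 3 p.m. On the rating it says: "Prior to each session, participants are asked to indicate their subjective level of sleepiness using the Karolinska Sleepiness Scale". On the samples: "Each session is followed by sample taking (blood, saliva, exhaled breath, dried blood spot". During the run itself "participants are asked to stay awake in a dark environment, either sitting still with open eyes without activation (M", or follow a car through a monotonous night drive in the simulator (D). Section 5.2 obtains the test latency by "averaging latencies from four max. 40 min test- sessions", so a run lasts up to 40 minutes and sleep onset is what it measures.

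Table 2 has the same order. KSS is the first item inside the session row ("Session 1/4 (KSS, DS-MWT or MWT, incl EEG and ET) | 45" minutes), and sampling is a separate row after it ("Sampling 1/4 (blood, saliva, exhaled breath, dried blood spots) | 15" minutes). There is no KSS after a run and no sample before one.

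In section 3.1, objective O_s-6 asks whether candidate sleepiness biomarkers "correlate to the prior treatment or withdrawal of CPAP and the outcomes of the ESS and KSS". Section 5.1.2 treats all secondary variables as hypothesis-generating. No section says which rating is to be paired with which sample.

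**The concern.** KSS rates sleepiness at the moment it is asked, and the protocol asks for it four times a day, so it evidently expects the value to move within a day. Between the rating and the sample lies a task designed to bring out sleepiness, in which the participant may fall asleep. The rating describes the participant before that task, and the sample describes the participant after it.

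If a marker follows current sleepiness, pairing it with the earlier rating weakens the association. If sleep during the run also differs between withdrawal and continuation, or between sitting and driving, the marker-KSS association could differ by condition for reasons of timing alone. A rating that was never taken at sampling cannot be recovered at analysis, so this has to be settled at data collection and cannot be left to an analysis plan.

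**Working it through.** **Inputs.** Table 2: session slot 45 min and sampling slot 15 min (sessions 1, 2 and 4), break 60 min. Sections 4.3 and 5.2: run up to 40 min. Section 4.3: starts every two hours, and about 4 hours of testing and sampling per test day.

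**The plan's own figures first.**
- Testing and sampling: 4 × (45 + 15) = 240 min = 4 h. With the bare run length, 4 × (40 + 15) = 220 min, also about 4 h. The stated figure is reproduced.
- Spacing of starts: 45 + 15 + 60 = 120 min, which matches the two-hour grid.

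**Gap between rating and sample, full run.**
- Rating to start of sampling: 40 min if the rating is given just before the run and sampling follows at once; 45 min if it is given at the start of the slot. So about 40 to 45 min.
- Rating to end of sampling: 40 + 15 = 55 min to 45 + 15 = 60 min.
- End of sampling to the next rating: the 60-min break. This exists for samples 1 to 3; no rating follows sample 4.
- Sample sets for a participant with four test days: 4 × 4 = 16, none with a concurrent rating.

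**The third session as printed.** Table 2 gives 15 min for session 3 and 75 min for sampling 3. A 15-min slot cannot hold a 40-min run. The sequence 15 + 75 + 60 = 150 min from 1 p.m. puts session 4 at 3:30 p.m., against the stated 3 p.m. The table's testing and sampling then sum to (45 + 45 + 15 + 45) + (15 + 15 + 75 + 15) = 150 + 120 = 270 min, against about 240. These entries must be reconciled with section 4.3. The order of rating and sampling is the same in that row, so the point does not depend on it.

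**Limits of the timing figures.** Forty minutes is a maximum. The protocol does not say whether a run stops at sleep onset; if it does, and sampling follows directly, some gaps before sampling are shorter.

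**Which analyses use KSS against a sample.**

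| Analysis | Uses KSS with a sample? |
| --- | --- |
| Primary: MWT against DS-MWT latency | No |
| O_s-6: biomarkers by CPAP condition | No |
| O_s-6: biomarkers with ESS | No |
| O_s-6: biomarkers with KSS | Yes |

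**The case against.** The strongest reply is that the reach is narrow and the harm unproven, and much of this stands.

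- *The analysis is exploratory.* True: section 5.1.2 promises cautious interpretation and expects independent validation. That limits the severity. It is not a reason to collect the two measures apart when a concurrent rating is nearly free.
- *Pairing is left open.* Also true. Samples 1 to 3 lie between two ratings, so day means or bracketing values could be used. But the bracketing ratings are 120 min apart, sample 4 has only the earlier one, and no such rule is stated.
- *The markers may move slowly.* Section 5.2 cites proteins that changed after 6 hours of sleep deprivation. If the markers reflect sleep pressure over hours, an offset of 40 to 45 min may matter little. The documents give no kinetics, so this can be neither accepted nor excluded.

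Two stronger readings are tempting and are not supported.

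- A reader might infer that the offset can create or hide biomarker differences between withdrawal and continuation, or between the two tests. It cannot, because those comparisons of levels do not use KSS. That sleep during the run differs by condition is itself an inference from the design, not something the protocol reports.
- A reader might also put a number on the loss. For example, if sleepiness before and after the run correlates 0.5 to 0.8, a true correlation of 0.50 would appear as 0.50 × 0.5 = 0.25 to 0.50 × 0.8 = 0.40. That range is assumed. The product also requires that the marker follows the state at sampling and relates to the earlier rating only through it. Neither is established, so these figures show the mechanism and are not an estimate.

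**Conclusion.** The point holds as a minor design weakness. Section 4.3 and Table 2 agree that every KSS precedes a run and every sample follows one, and O_s-6 plans to correlate the two. For a full run the offset is about 40 to 45 min to the start of sampling. The next rating is about 60 min after sampling ends, and there is none after the fourth sample. This arithmetic rests on the 45-min and 15-min slots applying to all four sessions, which the printed third-session durations contradict.

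The consequence is conditional. Marker-KSS associations may be weakened, and may differ by condition if sleep during the run does. How much cannot be derived from the protocol. A reader might take this as undermining O_s-6 as a whole; it does not, since its CPAP-condition and ESS parts, like the primary endpoint, are untouched.

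**What to change.** In section 4.3 and Table 2, add a second KSS at the start of each sampling slot, in every run of both tests. In O_s-6, name this post-run rating as the KSS correlate for the biomarkers. Keep the pre-run rating for relating to the latency of the run that follows. While editing Table 2, reconcile the session 3 and sampling 3 durations with section 4.3.

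Do not add sleep during the run as a covariate in the main model of biomarkers by CPAP condition. Such sleep may be a consequence of withdrawal, and adjusting for it could remove part of the effect that O_s-6 sets out to explore. At most, use it in a sensitivity analysis of the marker-KSS association.

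The cost is a rating of a few seconds per run (16 for a participant with four test days), inside an existing 15-min slot, plus one line in Table 2 and one field on the source form. The rating comes after the run, so it cannot affect the latency just measured. The downside is slightly more burden for participants.
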